## Abstract

**Background:**

Psychotic disorders contribute to significant morbidity and mortality partly due to the chronicity of the illness and high relapse rates. Delivering psycho-education messages about disease etiology, their signs and symptoms and the benefits of treatment adherence have been shown to improve clinical outcomes among individuals with psychoses. However, little has been done to examine the feasibility and efficacy of this intervention in low resourced settings.

**Objective:**

Our primary objective will be to determine the feasibility of recruiting and retaining patients with a first episode psychosis (FEP) and for the secondary objective, we will determine the preliminary efficacy of psycho-education on illness self-management, stigma, adherence to medications and symptom severity.

**Hypothesis:**

We hypothesize that (i) we will recruit 70% of eligible participants and accrue a sample size of 80 over 20-weeks, retaining 80% of the sample size for 24 weeks, (ii) the intervention will lead to improvement in clinical outcomes (described above).

**Methods:**

We will recruit 80 adult patients who have been diagnosed with a FEP, received antipsychotic medication at Butabika Hospital and reside within 21km from the Hospital. Trained village health team (VHTs) members will deliver 6 psycho-education sessions to 40 participants and their family members (intervention arm). Participants in the control arm (n = 40) will receive routine care. We will document how feasible it will be to recruit and retain participants over 24 weeks and document the preliminary efficacy of the intervention on illness self-management, stigma, adherence to medications and severity of symptoms.

**Data analysis:**

We will document the proportion of participants who consent and get recruited, the proportion of those who will get retained and reasons for drop out. We will conduct an intention to treat analysis comparing the groups at weeks 4, 12, 24 and assess the effect of the intervention on the clinical outcomes (described above). We will use the Bonferroni approach to correct for multiple comparisons.

**Trial registration:**

Clinical trials.gov registration number: NCT 04602585.

## Introduction

Psychotic disorders significantly contribute to the global burden of disease and disability, with sub-Saharan Africa (SSA) bearing a huge brunt of this burden [1–3]. For this study, we operationally defined psychosis as any of schizophrenia or schizophrenia spectrum disorder, brief psychotic episode, or bipolar affective disorders. Psychotic disorders have been shown to predict poor quality of life [4, 5], increased health care costs [6, 7], higher mortality mainly due to suicide, accidents, and comorbid infectious diseases [8–10] as well as non-infectious diseases like hypertension, obesity and diabetes mellitus [11–13] Literature shows a high prevalence of psychiatric illnesses such as depression, anxiety and substance misuse disorders [14–16] among patients with psychosis.

Due to the high burden of psychotic disorders, several scholars have recommended that it is identified and treated with antipsychotic medications—the main form of treatment. However, almost of half of individuals with psychoses relapse within 2–3 years of commencing treatment mainly due to poor medication adherence [17], yet long-term adherence is essential for ensuring the achievement of social and occupational functioning [18, 19]. The addition of interventions (adjunct) that are geared towards improving adherence to medication and stigma reduction have been shown to improve outcomes (retention in care and reduction in relapse) in persons taking antipsychotic medications [20, 21]. Psycho-education is among the most used adjunct intervention for individuals with psychosis—during these interventions, structured messages describing the aetiology of psychoses, their signs and symptoms, and the benefits of treatment are delivered. Most psycho-education studies have been conducted in high income countries (HIC) [20, 21] with little having been done in low resourced settings such as Uganda.

A number of factors makes it inappropriate to extrapolate findings from HIC to low resourced settings. First, inadequate funding for mental health interventions in resource constrained settings such as Uganda [22] means little may be done with regards to delivery of psycho-education—such activities may be considered extra workload. In the majority of low resourced settings, a prescription of antipsychotics (with little in the way of providing psycho-education) is the standard of care. Moreover, variations in clinical or symptom presentation, conceptualization of psychoses (negative explanatory models of psychosis and stigma), and disease severity in some ethnic groups across multiple populations in the world [21, 23–27] may dictate the way individuals accept treatment and ultimately influence the type of treatment that they receive [28]. Furthermore, the heterogeneous nature of psychoses including differences in responses to antipsychotics [25, 29–33] makes it inappropriate to extrapolate findings about the efficacy of psycho-education interventions from HIC to sub-Saharan Africa (SSA). Studies that examine culturally appropriate relapse intervention techniques are urgently needed.

### The problem

The high rates of relapse among individuals with psychoses only leads to higher rates of mortality (through suicide) and morbidity. With each relapse individuals will respond poorly to medications, stay longer [34] in hospital stay and lead unhealthy lifestyles—this will limit their longevity making it difficult to achieve multiple development milestones [35–37]. The need for relapse prevention interventions like psycho-education cannot be over emphasized. However the efficacy of adjunct therapies such as psycho-education remains to be known, as well as how feasible it is to recruit and retain participants for such interventions.

We propose to document the feasibility of recruiting and retaining persons with a first episode psychosis (FEP) and preliminary efficacy of a psycho-education intervention that will be delivered by village health team members (VHT). The operational definitions of a FEP varies widely [38], but for this study, individuals will be considered to have a FEP if they have (a) experienced psychotic symptoms for the very first time in their lives, (b) experienced psychotic symptoms before, but are accessing psychiatric care (antipsychotic medications) for the very first time in their lives at the study site, or (c) if already on antipsychotics or used antipsychotic medications for no longer than 6 weeks and (d) if the psychosis is not primarily a result of substance use disorders or a medical illness like HIV.

### Objective

Our primary objective will be to determine the feasibility of recruiting and retaining patients with a FEP and for the secondary objective, we will determine the preliminary efficacy of psycho-education on illness self-management, stigma, adherence to medications and symptom severity.

### Hypothesis

We hypothesize that (i) we will recruit 70% of eligible participants and accrue a sample size of 80 over 20-weeks, retaining 80% of the sample size for 24 weeks, (ii) the intervention will lead to improvement in clinical outcomes in patients with FEP (see above).

### The VHTs in the health care system

Village Health Teams (VHTs) were established by the Ugandan Ministry of Health in 2001 to empower communities to take part in the decisions that affect their health, mobilize communities for health programs, and strengthen the delivery of health services at house-hold level. Each VHT serves 25–30 households with a minimum of one third of VHTs per village being women. Potential VHT members may already be community health workers, traditional birth attendants, medication distributors or other individuals who are already providing adjunct care within the community. VHTs are chosen by popular vote and engage with members of the community through home visits and community dialogue with targeted messages. At least 4/10 people who reach the health centre are referred by the VHTs as per MOH reports of 2015.

In 2017, the MOH of Uganda trained VHTs in delivery of some aspects of mental health care using the WHO mhGAP—however, the feasibility of engaging them to deliver interventions for persons with psychosis is yet to be examined. For the proposed study, we will choose from among the MOH trained VHTs and train those who may have missed the MOH mental health training of 2017 to deliver psycho-education using materials described below.

### The psycho-education materials

The psycho-education materials consist of a combination of text and pictures that we developed through consultation with mental health specialists, patients and their caretakers. A number of psycho-education materials were developed for common mental disorders and psychosis in our earlier study [39]. We conducted qualitative interviews during the development of the documents. The psycho-education materials are being used for the very first time in the Ugandan setting.

Topics in the booklet (attached as S1 File) include information about i) The signs and symptoms of psychosis, ii) the challenges faced by people with psychosis including disruption in social and occupational functioning, iii) potential causes of psychosis (biological, substance use, trauma, stress), iv) the treatment options for psychosis(antipsychotics and adjunct psychosocial therapies) v) rationale for treating psychosis (reduction in relapse, improvement in ability to function), and vi) the myths about psychosis (dispelling stigmatizing undertones and challenging non-medical explanatory models of mental illness).

Each of the 6 topics lasts about an hour. To ensure standardization (all participants receive the same information), we converted the information into audio (English and Luganda). The VHT will play the audio as participants listen in and will then provide them with the written text for their future reference.

## Methods

### Study design

A pilot RCT to examine feasibility of recruitment and retention and preliminary efficacy of our intervention.

### Study setting

The study will be conducted at the Butabika National Mental Referral Hospital in Kampala, a 600 bed hospital located 13km east of Kampala city. The hospital has 3 acute admission wards, 3 convalescent wards (housing patients with less acute symptoms and ready for discharge), one male and one female sick ward (where individuals with physical illnesses are admitted), an alcohol and drug unit, a child and adolescent unit and a private wing. It has a medical out-patient that provides a service to HIV/AIDS patients, a dental clinic and a general out-patients’ clinic. The out-patient clinics operates weekdays from 9 am–5 pm. Each of the units (in-patient and out-patient) is run by team of psychiatrists, medical officers, psychiatric clinical officers (physician assistant with 3-year psychiatry training), psychiatric nurses, clinical psychologists and psychiatric social workers. We will recruit participants from the convalescent wards (clinically stable patients awaiting discharge).

#### Standard of care

At Butabika Hospital, patients with acute illnesses are admitted, treated with psychotropic medications and discharged usually over a 2-3-week period. The patients return to pick up their medications and get assessed by the clinician on duty. The clinician on duty could be a psychiatrist, medical officer or psychiatric clinical officer (an assistant physician equivalent). The patients receive little by way of psycho-education or any other form of psychological therapy—this is primarily due to the large numbers and few health care providers.

### Eligibility criteria

Individuals will be eligible if they have been diagnosed with a FEP and considered (by the attending clinician) to have demonstrable resolution of active symptoms following the use of antipsychotic medications and deemed clinically stable for a discharge. The FEP diagnosis will be confirmed through an interview conducted by a trained bachelors level research assistant (RA) using the Mini International Neuropsychiatric Instrument (M.I.N.I) [40]. Participants (adults ≥18 years) will be required to provide written informed consent and should reside within a 21 km radius from the hospital.

#### Exclusion criteria

Individuals will be excluded if they present with a psychosis secondary to a medical or substance use disorder.

### Sample size estimation

Being a study assessing feasibility of recruitment as a primary outcome, we have not conduced a formal sample size and power calculation. Rather, we have considered that recruiting 70% of potentially eligible participants over a 20-week period and retaining 80% of recruited participants will provide us with adequate data that will be needed in recruiting participants for a powered RCT.

In 2018 [41], a total of 43,870 individuals accessed care at the hospital, 60% (26,322) of them were diagnosed with psychotic disorders, approximately 20% (5,264) of the 26,322 patients with psychosis presented for the first time (potential cases of FEP). Thus, the number of participants who are eligible for recruitment is approximate 440 per month. Close to 20% of the Ugandan population lives within the central districts from where we intend to recruit participants—we anticipate having 88 patients (with psychosis) eligible for recruitment per week. However, a significant proportion of patients present with a psychosis resulting from substance use. We anticipate that approximately 40% of the 88 patients would be eligible as per criteria described below. Thus, we will have approximately 32 participants eligible for recruitment per week with a recruitment target of 24 of the 32 participants per week. We will document what proportion of this figure is attained.

With a sample size of 80 participants, we will be able to conduct preliminary analyses to detect modest significant differences (5% increase in mean scores) in illness self-management and adherence as well as a 5% reduction in mean stigma and symptom severity. We will use this data to generate an effect size that can be used in a sample size estimation of a powered RCT.

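### The recruitment estimate counts every hospital user, while the protocol is inconsistent on whether participants come from the wards only or also from out-patients; the eligible pool must be rebuilt for one stated source

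*Protocol article*

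**What the plan says.** The estimate is in the Protocol article, Sample size estimation. It begins with one year of hospital use: "a total of 43,870 individuals accessed care at the hospital, 60% (26,322) of them were diagnosed with psychotic disorders". About 20% of those with psychosis (5,264) are taken as first presentations, from which "the number of participants who are eligible for recruitment is approximate 440 per month". A 20% residence share follows, and "we anticipate having 88 patients (with psychosis) eligible for recruitment per week". A last share of 40%, introduced because many psychoses result from substance use, leads to a stated 32 eligible a week and a target of 24. The section says that attainment will be documented against this figure.

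Three other sections describe who can enter:

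- Study setting, on a hospital of 600 beds: "We will recruit participants from the convalescent wards (clinically stable patients awaiting discharge)".
- Eligibility criteria: the attending clinician must judge that symptoms have resolved on treatment and that the patient is "deemed clinically stable for a discharge".
- Participant identification and recruitment (Identification): out-patient departments are also informed, and eligible out-patients will be approached even if they may not be admitted.

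Standard of care adds that acutely ill patients are admitted, "treated with psychotropic medications and discharged usually over a 2-3-week period". The Hypothesis section sets the recruitment target: 70% of eligible patients, and 80 participants in 20 weeks.

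**The concern.** The pool in the estimate and the population in the entry rule are not the same. The estimate counts everyone who used the hospital, in-patient or out-patient. Two sections describe ward patients ready to leave, and a third adds out-patients. None of the shares in the estimate is a share admitted or ready for discharge, so the reader cannot tell which population the 32 a week describes.

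Recruiting 70% of eligible patients and 80 in 20 weeks is the first part of the study hypothesis, and the results are meant to inform a powered trial. If the benchmark comes from one population and the recruits from another, a shortfall could reflect the planning figure and not the feasibility of recruitment, and the same accrual rate could be carried into the later trial.

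**Working it through.** **Inputs.** From Sample size estimation: 43,870 users; shares of 60% (psychosis), 20% (first presentation), 20% (residence) and 40% (eligible); 32 eligible a week. From Study setting: 600 beds. From Standard of care: 2-3-week stay. From Hypothesis: 70% uptake, 80 in 20 weeks. The documents give no admissions count, no occupancy, and no psychosis or first-presentation share among in-patients.

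**1. The plan's own figure.**
- 43,870 x 0.60 = 26,322; x 0.20 = 5,264 a year; / 12 = 439 a month. These agree with the text.
- 440 x 0.20 = 88 a *month*, but the text says 88 a week.
- 0.40 x 88 = 35.2, where the text gives 32. The target of 24 out of 32 is 75%, not 70%.
- With the unit corrected: 5,264 x 0.20 x 0.40 / 52 = 8.1 eligible a week. The stated 32 is about four times this (32 / 8.1 = 4.0).

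**2. All-user base, unit corrected (out-patients count).** 8.1 x 20 = 162 eligible; x 0.70 = 113 recruited. The target of 80 is reachable.

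**3. What the wards can discharge.** At full occupancy, and with the 2-3-week stay applied to every bed:
- 600 / 3 = 200 and 600 / 2 = 300 discharges a week.
- x 52 = 10,400 to 15,600 a year, which is 24-36% of 43,870.

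**4. Ward-only ceiling, without the diagnostic shares.** Suppose every discharge were first-episode psychosis. Residence and eligibility alone leave:
- 200 x 0.20 x 0.40 = 16 a week.
- 300 x 0.20 x 0.40 = 24 a week.

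Both are below 32.

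**5. Ward-only, with all the plan's shares.** 0.60 x 0.20 x 0.20 x 0.40 = 0.0096.

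| | 3-week stay | 2-week stay |
|---|---|---|
| Discharges a week | 200 | 300 |
| Eligible a week | 1.92 | 2.88 |
| Eligible in 20 weeks | 38 | 58 |
| Recruited at 70% | 27 | 40 |
| Weeks to reach 80 | 60 | 40 |

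If occupancy ranged from 80% to 150% (an assumption), the figures would be 1.5-4.3 eligible a week and 22-60 recruited.

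**6. What 80 would need if ward-only.** 80 / 0.70 / 20 = 5.7 eligible a week.
- First-presentation psychosis as a share of discharges: 5.7 / (300 x 0.08) = 24% to 5.7 / (200 x 0.08) = 36%, against 0.60 x 0.20 = 12% among all users.
- Or, keeping the 12%, a local share of 5.7 / (300 x 0.12 x 0.40) = 40% to 5.7 / (200 x 0.12 x 0.40) = 60%, against 20%.
- Or, starting from the all-user chain, 5.7 / 8.1 = 71% of otherwise eligible patients passing through the wards.

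**The case against.** A reader might infer that 80 in 20 weeks is unreachable. The case against that inference is strong, and most of it stands.

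- **Out-patients.** The Identification section includes them, and Eligibility criteria do not say that the discharge must be from a ward. If they count, the all-user base is not wrong on this ground, and 80 is within reach once the unit is corrected. This stands. It does not settle the matter, because out-patients must still be eligible and the entry rule includes stability for discharge, which is not defined for someone never admitted.
- **In-patient mix.** The 60% and 20% shares are stated for all users. Admitted patients are described as acutely ill, so first-presentation psychosis may be more common among them. Beds do not prevent this: all 5,264 first presenters, about 101 a week, would be 34-51% of 200-300 discharges, above the 24-36% needed. This stands, so the 2-3 a week is conditional.
- **Residence share.** The 20% is a share of the national population. The share among this hospital's patients could be larger, so the ward-only shortfall cannot be called independent of it. This stands.
- **Bed turnover.** Full occupancy is an assumption. The 2-3-week stay is described as usual for acute admissions, yet it is applied here to all 600 beds, including the child, alcohol and drug, sick and private units. At 150% occupancy the ceiling in step 4 would be 24-36, so 32 would fall inside it, though only if at least 32 / 36 = 89% of discharges were first-episode psychosis.
- **The 40% share.** It could be read as absorbing the discharge condition, since it refers to the eligibility criteria in general. The only reason the text gives for it is substance-related psychosis.

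**Conclusion.** The point holds as an inconsistency in the source population with a conditional numerical consequence. The estimate uses all hospital users; Study setting and Eligibility criteria describe ward patients ready for discharge; Identification adds out-patients; and no step deals with admission.

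If recruitment is ward-only, the stated 32 a week cannot be met under the plan's residence and eligibility shares: the ceiling is 16-24, given full occupancy and a 2-3-week stay in all beds. Carrying over the remaining shares gives about 2-3 a week and 27-40 recruited in 20 weeks at 70%. That further step also assumes that the all-user mix holds for in-patients, which the documents do not say. If out-patients count, the corrected figure is about 8.1 a week and 113 recruited.

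The documents therefore do not show that 80 in 20 weeks is out of reach, nor that the trial will wrongly report recruitment as infeasible. They show that the target cannot be judged until the source is fixed and counted. The planning paragraph should be corrected, since it supplies the benchmark for a primary feasibility aim.

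**What to change.** 1. Reconcile Study setting, Eligibility criteria, Sample size estimation and Identification on one source population.
2. Rebuild the estimate from counts for that source. For the wards, use weekly discharges of adults with psychosis from the hospital discharge register, then apply first-presentation, residence and substance-use shares that relate to those patients. If never-admitted out-patients are included, show them on a separate line, with an entry condition that is defined for them.
3. Restate the weekly eligible number in consistent units, together with the number expected in 20 weeks or the weeks needed for 80.
4. Judge recruitment against the restated figure.

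The cost is one rewritten planning paragraph, a request for register counts, aligned wording on the source, and possibly a less favourable accrual figure. No extra patients or study procedures are needed.

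### The weekly recruitment forecast uses the national population share of undefined central districts, while eligibility requires residence within 21 km of the hospital

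*Protocol article*

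**What the plan says.** Two sections of the protocol article set the residence rule. Under Eligibility criteria, participants "should reside within a 21 km radius from the hospital". The Methods paragraph of the abstract likewise describes adults who "received antipsychotic medication at Butabika Hospital and reside within 21km from the Hospital".

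The section Sample size estimation builds a recruitment forecast from 2018 hospital figures: "a total of 43,870 individuals accessed care at the hospital", "60% (26,322) of them were diagnosed with psychotic disorders", and about 20% of the latter (5,264) presented for the first time. It concludes that "the number of participants who are eligible for recruitment is approximate 440 per month". It then narrows this number geographically, because "Close to 20% of the Ugandan population lives within the central districts from where we intend to recruit participants", and arrives at 88 patients per week. After a remark on substance-related psychosis it keeps about 40% as meeting the eligibility criteria, which gives 32 eligible per week and a target of 24. It closes the forecast with "We will document what proportion of this figure is attained".

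The 21 km radius does not appear in this section. No part of the article says which districts are meant or how they relate to the radius.

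**The concern.** There are two separate mismatches in the 20% step.

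- **Area.** The trial admits people from a circle around the hospital. The forecast counts people from a set of districts, and nothing shows that the two areas coincide.
- **Denominator.** The 20% is a share of Uganda's population, but it multiplies a count of patients who already attend this hospital. That is valid only if those patients are spread over the country as the general population is, which the article neither states nor supports.

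Feasibility of recruitment is part of the primary objective, and the plan says that attainment against the forecast will be documented. If the residence fraction is not the one that eligibility imposes, a gap between forecast and attainment mixes two things: how well recruitment went, and how far the assumed fraction was from the true one. A later powered trial that borrows the forecast would inherit the same ambiguity.

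**Working it through.** **Inputs**, all from Sample size estimation unless stated: 43,870 attenders in 2018; 60% with psychosis; 20% of those presenting for the first time; geographic factor 20%; eligibility factor 40%; 32 eligible and 24 targeted per week. From the Hypothesis section: 70% of eligible patients recruited, and 80 participants in 20 weeks.

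**Step 1: reproduce the plan's figures.**
- 43,870 × 0.60 = 26,322; × 0.20 = 5,264 per year; / 12 = 438.7 per month. The stated 440 reproduces.
- 440 × 0.20 = 88. The geographic factor is therefore in use, but 88 is a monthly figure and the article labels it weekly. Per week it is 5,264 / 52.18 × 0.20 = 20.2, so the label inflates the pool by 52.18 / 12, about 4.3.
- 88 × 0.40 = 35.2, not 32.

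These two slips are separate from the geographic mismatch. The next steps use the corrected time unit so that the geographic point stands alone.

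**Step 2: express the pool through the residence share.** Let *g* be the fraction of the hospital's first-presentation psychosis patients who live within 21 km. Read the 40% as excluding residence.
- First presentations per week: 5,264 / 52.18 = 100.9
- Eligible per week: 100.9 × 0.40 × *g* = 40.4 × *g*
- Recruited in 20 weeks at 70%: 40.4 × *g* × 20 × 0.70

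The documents do not give *g*. The range below is an assumption. Results are from unrounded values.

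| *g* | Eligible per week | Recruited in 20 weeks at 70% |
|---|---|---|
| 10% | 4.0 | 56 |
| 20% (the plan's factor) | 8.1 | 113 |
| 40% | 16.1 | 226 |

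**Step 3: share needed for 80 in 20 weeks.** Eligible patients needed per week: 80 / 20 / 0.70 = 5.7. Required *g* = 5.7 / 40.4 = about 14%.

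**Step 4: the other reading of the 40%.** If the 40% already covers every criterion, residence included, *g* cannot be separated out. What matters then is the overall fraction of first presentations that is eligible. The plan implies 0.20 × 0.40 = 8%; the target needs 5.7 / 100.9 = about 5.7%. On this reading the table in Step 2 would count residence twice and should not be used.

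**The case against.** The strongest reply is that the forecast does not end with the district share. The 40% step is worded as applying the eligibility criteria, and the 21 km rule is one of them, so the final weekly number may already reflect the radius. This stands as an ambiguity. The only reason the text gives for the 40% is substance-related psychosis, and if residence is also inside it, geography is filtered twice on two definitions. Either way the 20% remains a share of the wrong kind.

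A second reply is that this is a rough planning proxy, hedged as approximate, for a hospital that serves the nation. That is fair as to its weight: it is an unsupported input, not a miscalculation. The demonstrable numerical fault in the same paragraph is the monthly figure labelled weekly.

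A reader might go further and infer three things that the documents do not support.

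- *That the target of 80 in 20 weeks is derived from this pool.* It is not. The section says that no formal sample size calculation was made, and the stated forecast would give 32 × 20 = 640 eligible and 24 × 20 = 480 recruited.
- *That the feasibility results become uninformative.* The hypothesis and the data analysis plans concern the proportion of eligible patients who are recruited, the duration of recruitment and retention. Data collection counts eligible patients who agree to enrol. None of these uses the 20%.
- *That the pool is overstated, or understated.* A circle smaller than the districts would lower it. If people living near the hospital are over-represented among its patients, that would raise it. The article has no figure for either.

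**Conclusion.** The mismatch is real and limited in reach. The residence fraction behind the forecast of 32 eligible and 24 targeted per week is not an estimate of the fraction that the eligibility criteria impose, and the plan intends to report attainment against that forecast. It is not established that the final weekly figure describes a wholly different population, because the 40% step may absorb part of the radius.

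No corrected value can be given. At the plan's own 20%, with the time unit put right, the target is reachable: 113 against 80. It would be missed only if fewer than about 14% of first presentations live within 21 km. That threshold rests on the 2018 volumes, the stated 40% read as excluding residence, and 70% uptake; nothing in the documents says on which side of it the true share lies. Reconciling the geography alone would leave the benchmark wrong, since the month-to-week slip of about 4.3-fold sits in the same figures.

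**What to change.** Keep the 21 km criterion and bring the forecast into line with it.

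1. In Sample size estimation, replace the 20% national share with the fraction of the hospital's first-presentation psychosis patients whose recorded address lies within 21 km.
2. If past addresses cannot be used for this (the article does not say whether they can), report attainment against the eligible patients within 21 km who are counted in the trial's own screening.
3. State whether the 40% covers residence or only the other criteria, so that residence is counted once.
4. Restate the eligible and target figures per week in the same revision that corrects the monthly number labelled weekly.

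The cost is a small tabulation and a restated benchmark, with no change to participants or procedures. The alternative of widening the residence criterion to the districts is not free: it would change who is enrolled and where the village health teams deliver sessions.

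### The recruitment projection carries a monthly count forward as a weekly one, so the target of 24 recruits per week is wrong and fits neither the sample of 80 nor the 20-week window

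*Protocol article*

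**What the plan says.** The Protocol article, Sample size estimation, builds its recruitment projection in a chain.

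- It starts from 2018 hospital activity: "a total of 43,870 individuals accessed care at the hospital", of whom "60% (26,322) of them were diagnosed with psychotic disorders". About 20% of these, 5,264, were first presentations.
- It converts this to months: "Thus, the number of participants who are eligible for recruitment is approximate 440 per month".
- It applies a share of close to 20%, described as the part of the Ugandan population living in the central districts, and states: "we anticipate having 88 patients (with psychosis) eligible for recruitment per week".
- It expects about 40% of the 88 to meet the criteria, mainly because many psychoses result from substance use, and arrives at "approximately 32 participants eligible for recruitment per week with a recruitment target of 24 of the 32 participants per week".
- It closes with: "We will document what proportion of this figure is attained".

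The Hypothesis section sets the feasibility targets separately: "we will recruit 70% of eligible participants and accrue a sample size of 80 over 20-weeks", with 80% retained for 24 weeks. Sample size estimation repeats the 70%, the 20 weeks and the 80% retention as the justification for the study size, and says that no formal calculation was made.

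**The concern.** Feasibility of recruitment is the primary objective, and this chain is the plan's only quantitative account of how many patients will be available. The time unit changes from month to week at the catchment step with no division to support it, and the weekly unit then carries through to the eligible pool and the recruitment target. The 24-per-week target therefore cannot stand beside 80 patients in 20 weeks, yet the plan undertakes to report attainment against it. A reader of the results would meet two benchmarks that give very different accounts of the same accrual: one fully met, the other missed by a factor of six.

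**Working it through.** **Inputs**, all from Sample size estimation unless noted: 43,870 attendances in 2018; 60% with psychosis; 20% of those first presentations; 20% catchment share; 40% meeting the criteria; stated results 88, 32 and 24 per week. From Hypothesis: 70% uptake, sample of 80, 20 weeks.

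**1. Reproduce the plan's chain.**
- 43,870 × 0.60 = 26,322, as stated.
- 26,322 × 0.20 = 5,264 per year, as stated.
- 5,264 / 12 = 438.7 per month, stated as about 440.
- 438.7 × 0.20 = 87.7 per month. The figure 88 reproduces, but as a monthly count.

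**2. Look for a route to 88 per week.**
- 5,264 / 52 × 0.20 = 20.2 per week.
- 88 × 12 / 52 = 20.3 per week.
- 88 / 4 = 22 per week, with four-week months.
- 5,264 / 52 = 101 per week, with no catchment share.

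None gives 88. The overstatement is 88 / 22 = 4.0 to 88 / 20.25 = 4.35 times.

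**3. Check the next two steps.**
- 0.40 × 88 = 35.2, against the stated 32 (32 / 88 = 36.4%).
- 24 / 32 = 75%, against the hypothesised 70%. With the product corrected, 24 / 35 = 69%.

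**4. Compare the weekly target with the trial, as written.**
- 24 × 20 = 480 recruits; 480 / 80 = 6.
- Attainment if all 80 enrol in 20 weeks: 80 / 480 = 16.7%.
- Time to 80 at 24 per week: 80 / 24 = 3.3 weeks. Rate needed for 80 in 20 weeks: 80 / 20 = 4 per week.

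**5. Repeat with the unit corrected.**
- Eligible: 87.7 × 0.40 = 35.1 per month; × 12 / 52 = 8.1 per week.
- 24 / 8.1 = 3.0, so the weekly target is about three times everyone eligible.
- At 70% uptake: 35.1 × 0.70 = 24.6 per month, or 8.1 × 0.70 = 5.7 per week.
- Time to 80: 80 / 5.67 = 14.1 weeks. If the stated 32 is kept and read as monthly, eligible is 32 × 12 / 52 = 7.4 per week, and 80 takes 80 / (0.70 × 7.38) = 15.5 weeks.

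Read as a monthly figure, 24 is close to 70% of 35. This suggests that the target was meant per month, but the text does not say so.

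**The case against.** The strongest reply is that the error does not reach the feasibility results themselves, and most of that reply stands.

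A reader might infer that the primary feasibility result cannot be read. The documents do not support this. The abstract's Data analysis paragraph, Data collection and Data analysis plans all base recruitment on counts made during the study: eligible patients who accept, duration of recruitment, and the proportion of eligible patients recruited. Retention is also observed directly. None of these uses 88, 32 or 24 as a denominator.

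A reader might also infer that a trial enrolling 80 on time would be declared a failure. No pass or progression rule is attached to the weekly figure; the plan undertakes only to document attainment. Nor need the planned powered trial inherit the error, since the quantities to be reported are observed ones.

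It is also tempting to say that 70% uptake, 80 patients and 20 weeks conflict even after correction, because 8.1 × 20 = 162 eligible and 80 / 162 = 49%. That holds only if every eligible patient over the full 20 weeks forms the denominator and enrolment ends at exactly 80. If 20 weeks is a limit, the three targets are compatible.

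Finally, the 75% is probably not an independent error: it disappears once 32 becomes 35.

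The reply leaves untouched the wrong unit, the wrong product, and a stated weekly target that cannot be reconciled with the sample and the window.

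**Conclusion.** The projection is wrong as written. The catchment pool is overstated 4.0 to 4.35 times, the eligible count is also miscalculated, and the target of 24 per week is six times what the sample of 80 over 20 weeks implies. On the corrected figures it is about three times the eligible pool. The damage is confined to the projection and to the attainment measure tied to it; observed uptake, duration and retention are unaffected.

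The corrected values take the plan's 60%, 20%, 20% and 40% at face value. The catchment share is itself an assumption: it describes where Ugandans live, not where this hospital's patients live, and it is not the 21 km radius in Eligibility criteria. So about 8 eligible per week is what the plan's own inputs imply, not an established pool, and the 14 weeks is equally provisional. The unit error does not depend on these assumptions.

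**What to change.** In Sample size estimation:

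1. Restate the projection as 88 per month, about 35 eligible per month (about 8 per week), and about 24 to 25 recruits per month at 70% uptake. Say that the 20% catchment share is an assumption.
2. Remove the 24-of-32-per-week target and the commitment to report attainment against it.
3. Put two separate benchmarks in its place: accrual of 80 within 20 weeks (at least 4 per week on average), and uptake of 70%.
4. State that the uptake denominator is patients actually screened and found eligible up to the 80th enrolment, not the projected pool.

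The cost is protocol wording only. The sample of 80, the design, the outcomes and the data to be collected do not change. The stated pool becomes about four times smaller, but on the plan's own inputs it still suffices for 80 patients within 20 weeks at 70% uptake.
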